### Monitoring

2.10

An electronic case report form (eCRF) has been created using the RedCap computer platform. IDIBELL Clinical Research and Clinical Trials Unit (UICEC-IDIBELL) is carrying out the monitoring of the trial. Regular monitoring is performed by the UICEC IDIBELL according to the ICH GCP. Compliance with the approved protocol and verification of data is evaluated according to applicable regulatory requirements. The key data in the Monitoring Plan are those related to informed consent, primary outcome, mortality and safety data.

### Adverse events reporting and quantification

2.11

#### Definitions

2.11.1

●*Adverse event (AE)*: any injury related to medical management (including all aspects of care) that occurs during the patient's participation in the clinical trial will be considered an adverse event. An adverse event may be related to the study medication or be non-related.●*Adverse drug reaction (AR): any ‘adverse drug event’ that occurs when the medication is used as directed and in the usual dosage will be considered an adverse drug reaction.*●Serious AE (SAE) or serious AR (SAR) are considered to be those that at any dose:-provoke death (Note: death is a possible evolution of SARS-CoV-2 infection);-put patient's life at risk;-require the patient's hospitalization or the extension of an existing hospitalization.-cause permanent or significant disability or incapacity;-cause a congenital anomaly or malformation;-are considered medically relevant.●*Adverse drug event of particular interest for the study*: The investigator shall record in the eCRF and communicate to the promoter, the AE that are considered of special interest as soon as possible and no later than 15 days after he becomes aware of them. The AEs that are considered of special interest are:-refractory hypertension (defined as poor blood pressure control despite 3 antihypertensive drugs including a diuretic);-renal impairment (decrease of more than 50% of the GFR compared to the baseline);-ventricular tachycardia.

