#### Statistical considerations

2.9.2

A descriptive analysis of the study variables will be carried out. Continuous variables will be described as mean and Standard Deviation (SD) or as median and range; and categorical variables as absolute frequencies and percentages. The main analysis will be performed when all patients reach clinical stability or failure. If patients are in hospital for 56 days, they will be considered clinical failures. Comparison between average time to achieve clinical stability between the two study groups will be measured using the log-rank test. To quantify the degree of association, hazard ratio will be estimated with a Cox proportional hazards model using a 95% confidence interval.

Efficacy analyses will be performed for the intention to-treat (ITT) population. If a proportion of subjects >10% is detected to have relevant deviations from the protocol (for example, non-compliance with the selection criteria, non-compliance or inability to receive the trial treatment), the per protocol (PP) analysis will exclude those subjects with such deviations. If this group is defined, all exploratory efficacy analyses will be repeated as a sensitivity test.

As additional analysis, a Cox proportional hazards model, adjusted for clinically relevant confounding factors such as age, sex, comorbidities using the Charlson index, indexes to assess the severity of pneumonia (PSI and CURB-65), index of organic dysfunction (SOFA) and inflammatory parameters will be performed. In addition, prespecified subgroup analyses involving sensitivity analysis will be used to evaluate outcomes in patients not receiving invasive mechanical ventilation.

For evaluation of secondary variables, we will calculate unadjusted and adjusted estimations of effect size and the corresponding 95% confidence intervals using linear, logistic or proportional hazards Cox regression. Study adverse events will be described according to their severity and relationship with other treatments, and will be compared between treatment groups. Midway through recruitment, i.e. 21 patients per arm, an intermediate efficacy and safety analysis will be performed. For this, a correction of the type I error will be applied following Lan-DeMets (O'Brien – Fleming) in evaluation of efficacy.

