#### Reporting

2.11.2

The UICEC-IDIBELL is carrying out pharmacovigilance of the trial. All SAEs (including death), regardless of their relationship with the investigational medications, have to be notified by the investigator within 24h. The investigator has to make the notification via the SAE Notification Form, sending it by email to the pharmacovigilance unit that will review it and, if appropriate, will request additional information from the investigator. The investigator will provide information to the promoter or pharmacovigilance unit whenever requested and, in any case, when its initial evaluation changes regarding severity or causation. Likewise, all additional information regarding the AE, until the end of the study or until its definitive outcome, must be communicated without delay, via follow-up reports following the notification procedure previously described.

In case of a suspected unexpected serious adverse reaction (SUSAR), UICEC-IDIBELL will report to the competent authorities. The sponsor will also report the development update safety report (DSUR) once a year to the ethics committee and the Spanish Agency for Drugs and Health Products (10.13039/501100007761AEMPS).

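### The adverse-event definition requires a link to medical care, so non-fatal events put down to COVID-19 can go unrecorded and the safety comparison is open to bias

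*Protocol article*

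**What the plan says.** Section 2.11.1 (Definitions) of the protocol article describes an AE as "any injury related to medical management (including all aspects of care", arising while the patient takes part in the trial. The next sentence adds: "An adverse event may be related to the study medication or be non-related". Seriousness is then defined on top of that: "Serious AE (SAE) or serious AR (SAR) are considered to be those that at any dose" meet one of the listed criteria. Death is one of them, with the remark "Note: death is a possible evolution of SARS-CoV-2 infection". An adverse drug reaction (AR) is confined to events occurring "when the medication is used as directed and in the usual dosage".

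Section 2.11.2 (Reporting) requires: "All SAEs (including death), regardless of their relationship with the investigational medications, have to be notified by the investigator within 24h".

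On analysis, Section 2.9.2 states: "Study adverse events will be described according to their severity and relationship with other treatments, and will be compared between treatment groups". It also plans an interim efficacy and safety analysis at 21 patients per arm. The Discussion says that this interim look will cover adverse events potentially related to immunosuppression. The trial is open-label, and only the analysts are blind.

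**The concern.** The definition puts a judgement about cause ahead of recording. A clinician who believes that a complication is the viral illness, and not a consequence of any care given, has by the letter of the text no AE to enter.

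That judgement is hard in this population, because progression of severe COVID-19 and harm from immunosuppression can look alike. The Discussion itself concedes that opportunistic infections are hard to assign to any one drug. The people judging know the allocation, and the experimental arm has two additional drugs that could be held responsible. Section 2.5 also makes severe infection a reason to stop experimental treatment. That can apply in one arm only, so it gives staff a one-sided reason to look for infection.

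Safety is a joint objective with efficacy. If the share of events passing the cause filter differs between arms, the AE comparison mixes incidence with attribution. Blinding the analysts cannot recover events that were never entered.

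**Working it through.** **Step 1. Does any sentence lift the condition?** Two candidates exist.

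- The sentence after the AE definition says that an AE may be unrelated to the study medication. This removes the link to the drug and leaves the link to medical management in place.
- The 24-hour rule in Section 2.11.2 applies whatever the relationship to the investigational medications. It fixes which SAEs must be notified and, apart from naming death, does not widen what an SAE is. An SAE is an AE or AR that meets a seriousness criterion, so it carries the same condition.

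For non-fatal events, neither sentence lifts it.

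**Step 2. Which events are exposed?**

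| Event | Required as AE/SAE as written? | Other capture |
|---|---|---|
| Death | Yes, named in 2.11.2 | All-cause mortality at days 28 and 56 (2.8.2) |
| Refractory hypertension, GFR fall above 50%, ventricular tachycardia | Yes, listed for recording as special-interest AEs with no cause condition in the items, although the heading speaks of drug events | Creatinine three times a week in hospital (2.7.2) |
| Need for ventilatory support | Depends on judged cause | Counted as a secondary endpoint (2.8.2) |
| Non-fatal infection judged to be COVID-19 | No | No special-interest listing and no endpoint of its own |
| Other non-fatal events judged to be COVID-19 | No | Only as far as they show on the 8-point scale or in laboratory values |

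The treatment-failure rule in Section 2.8.1 uses grade 3 or 4 events attributed to trial treatment. Such events already have a link to care, so the AE definition does not remove them.

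**Step 3. How would differential attribution act?** The plan gives no AE rate, so there is no stated figure to reproduce. Let p be the true event rate in an arm and a the share of events that staff put down to care. Then:

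- recorded rate = p × a
- recorded risk ratio = (p_E / p_C) × (a_E / a_C)

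The arm size is 42 (Section 2.9.1). All values of p and a below are assumptions chosen to show a range. E is experimental, C is control.

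| True rate E / C | Share recorded E / C | Recorded rate E / C | Expected patients of 42, E / C | Recorded ratio (true) | Recorded difference (true) |
|---|---|---|---|---|---|
| 20% / 20% | 80% / 60% | 16% / 12% | 6.7 / 5.0 | 1.33 (1.0) | 4 points (0) |
| 50% / 50% | 80% / 60% | 40% / 30% | 16.8 / 12.6 | 1.33 (1.0) | 10 points (0) |
| 20% / 20% | 90% / 50% | 18% / 10% | 7.6 / 4.2 | 1.80 (1.0) | 8 points (0) |
| 45% / 30% | 60% / 90% | 27% / 27% | 11.3 / 11.3 | 1.0 (1.5) | 0 points (15) |
| 45% / 30% | 60% / 60% | 27% / 18% | 11.3 / 7.6 | 1.5 (1.5) | 9 points (15) |

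The filter can therefore create an apparent excess, hide a real one, or leave the ratio intact. With equal shares below 100%, the ratio is right but the absolute difference shrinks. At the interim, with 21 per arm, the expected counts halve (third row: 3.8 against 2.1), so a few differently classified events would change the picture.

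**Step 4. Adverse reactions.** An AR must arise at usual dosage, yet a serious AR, which is a kind of AR, is counted at any dose. The two phrases stand in the same list and do not fit together. No usual dosage is stated for tacrolimus, which Section 2.5 individualises by blood level.

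**The case against.** The strongest reply is that the wording is loose but most serious harm is caught anyway. Care in all its aspects is a broad term, and many investigators would record generously. AE registration is scheduled at every visit in Table 1. Relationship to treatment is already reported apart from severity, the planned comparison is not limited to drug-related events, and monitoring follows ICH GCP with safety among the key data. The article also condenses a complete protocol, accepted in May 2020 and not shown, so actual recording practice cannot be judged from it. All of this is fair. It limits the point without removing it: how generously to record is left to each unblinded judgement, and the definition is what the article itself states.

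Three stronger readings are tempting, and the document does not support them.

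- **That deaths, renal failure and arrhythmia drop out.** Death is named in the reporting rule and is an endpoint in its own right. A GFR fall above 50% and ventricular tachycardia are on the special-interest list, which tells the investigator to record them.
- **That the safety comparison is shown to be biased, or biased against the experimental arm.** The article gives no attribution shares. Equal shares leave the ratio unchanged, and unequal shares could push it either way.
- **That reactions above the usual dosage escape reporting.** An injury from excess dosing is plainly related to medical management, so it is an AE. If serious, it must be notified within 24 hours and is reviewed by the pharmacovigilance unit. What remains is an inconsistency of wording.

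**Conclusion.** The point holds in limited form. As written, Section 2.11.1 lets non-fatal events attributed purely to COVID-19 stay out of the AE and SAE data, and no other provision closes that gap for infections. The between-arm AE comparison in Section 2.9.2 and the interim safety review are therefore open to bias of unknown size and direction.

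The conclusion rests on reading the definition literally and on attribution being made by staff who know the allocation. It does not rest on the assumed rates above, which show only the mechanism. No design figure is affected and the sample size stays at 84. This should be corrected because it concerns a stated definition behind a planned comparison, but it does not undermine the mortality, ventilation or special-interest data. The mismatch in the AR wording is minor.

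**What to change.** 1. In Section 2.11.1, define an AE as any untoward medical occurrence in a randomised patient during participation, whatever its cause and in the same words for both arms. SAEs then follow from the seriousness criteria without a cause filter.
2. Keep relationship to treatment as a separate field, completed after the event is entered and never a condition for entering it.
3. In Section 2.9.2, base the between-arm comparison, including the interim one, on all AEs and all SAEs regardless of attribution. Present attributed events as a supplementary description.
4. Reconcile the usual-dosage wording for ARs with the any-dose wording for serious ARs.

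The cost is a change of wording in the protocol and eCRF guidance, and somewhat more events to record, since disease progression will now be entered. Because the article reports that recruitment is under way, patients already enrolled would need a chart check for non-fatal events passed over, done alike in both arms.

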#### Reporting

2.11.2

The UICEC-IDIBELL is carrying out pharmacovigilance of the trial. All SAEs (including death), regardless of their relationship with the investigational medications, have to be notified by the investigator within 24h. The investigator has to make the notification via the SAE Notification Form, sending it by email to the pharmacovigilance unit that will review it and, if appropriate, will request additional information from the investigator. The investigator will provide information to the promoter or pharmacovigilance unit whenever requested and, in any case, when its initial evaluation changes regarding severity or causation. Likewise, all additional information regarding the AE, until the end of the study or until its definitive outcome, must be communicated without delay, via follow-up reports following the notification procedure previously described.

In case of a suspected unexpected serious adverse reaction (SUSAR), UICEC-IDIBELL will report to the competent authorities. The sponsor will also report the development update safety report (DSUR) once a year to the ethics committee and the Spanish Agency for Drugs and Health Products (10.13039/501100007761AEMPS).

### Ethical considerations

2.12

This trial conforms to the Declaration of Helsinki and Good Clinical Practice guidelines, and personal data protection as required by Spanish law (LOPD 3/2018). The protocol and informed consent form (ICF) were approved by the BUH's Ethical Committee for Drug Research (EC) and by the Spanish Agency for Drugs and Health Products (AEMPS) in March 2020, in accordance with current legislation, Royal Decree 1090/2015 of December 4 and European Regulation 536/2014 of April 16, regulating clinical trials with drugs.

The patient, his or her closest legal or family representative (in case of incapacity due to the severity of the clinical situation) has to accept the ICF. As patients with COVID-19 can infect researchers via the ICF document, patients can consent orally with a witness, and this is documented in the patient's medical history. If the legal representative or a close relative is in quarantine due to COVID-19 quarantine, informed consent is provided orally by telephone and documented in the patient's medical history. The written ICF is obtained when the patient or his/her closest legal or family representative are able to give consent, as they are not quarantined.

Methylprednisolone and tacrolimus are commercially available as generic drugs, so no special permissions are required. Both the promoter and the center are respectively responsible for the treatment of patient data and commit to comply with Regulation (EU) 2016/679 of the European Parliament and of the Council of April 27, 2016 on Data Protection (RGPD), as well as with all other laws and regulations in force and applicable (Organic Law on Protection of Personal Data and Guarantee of Digital Rights 3/2018 of December 05). The data collected for the study are identified by a code, so as not to include any information that can identify the patient (name, surname, initials, address, social security number, etc.). Only the study clinician/collaborators are able to relate such data to the patient and his/her medical history. Therefore, a patient's identity is not revealed to any other person except the health authorities when required, or in the case of medical emergency. Access to patient information is restricted to the attending physicians, the health authorities AEMPS, the Clinical Research Ethics Committee, and personnel authorised by the sponsor when they need to check the data and procedures used in the study, always maintaining confidentiality in accordance with current legislation. If participants wish to know more, they can contact the Promoter's Data Protection Officer.

#### 1 Protocol amendments

2.12.1

The protocol was approved by the EC and the AEMPS on March 31, 2020, in a process of authorization adapted to the pandemic situation and based on a protocol synopsis (March 28, 2020). A substantial amendment to the original protocol was submitted to the EC and the AEMPS in accordance with Spanish legislation, and accepted on April 9, 2020. We decided to reduce tacrolimus plasma levels from 10 to 15 to 8–10 ng/mL and not to maintain corticosteroids by protocol beyond the three pulses of methylprednisolone in the experimental group. In addition, some exclusion criteria were added, such as glomerular filtration ≤30 mL/min/1.73m2, leukopenia ≤4000 cells/μL or other conditions that cause immunosuppression, and concomitant and potentially serious infections. Another additional amendment was accepted by the EC and AEMPS on May 25, 2020, including a complete clinical study protocol with new secondary key outcomes (8-point Ordinal scale and radiological abnormalities) that are being analysed in several COVID-19 clinical trials. These outcomes are being prospectively reported in the trial's eCRF, but were not reported in the protocol synopsis. We do not remove any of the previous key study outcomes.

### Publication plans

2.13

The trial is currently actively recruiting patients. Completion of patient recruitment is expected for Q3-Q4 of 2020. The sponsor commits itself to publishing the data within 12 months of completion of the study. Results will be analysed and reported in accordance with CONSORT guidelines.

## Discussion

3

Clinically, COVID-19 patients can evolve into 3 stages of progressive severity. Viral incubation and early establishment of the disease are the predominant components in the first week from the onset of symptoms. In the second stage, viral replication and transition into moderate acute lung involvement are the most important components. The third and most advanced stage manifests as severe pulmonary injury and systemic multi-organ failure, resulting from cytokine storm and systemic hyperinflammatory response. Older age, comorbid chronic conditions, elevated body mass index, lymphopenia, and elevated transaminases, LDH, D-dimer, ferritin, and soluble IL-2 receptor (sIL-2R) on admission are some of the reported risk factors associated with higher mortality [[7], [8], [9], [10], [11], [12]]. From a pathological viewpoint, two different pathological mechanisms appear to coexist in the COVID-19 illness; the first, triggered by the virus itself, and the second, by the host-immune response. Accordingly, a two-step sequence of antiviral and anti-inflammatory drug administration has been proposed, regarding the natural 3-stage evolution of COVID-19 disease [19].

Despite randomized clinical trials (RCTs) being the only way to find effective and safe treatments, very limited available RCTs for treating COVID-19 have been reported to date [20]. Given the emergency situation, most patients are receiving compassionate, unproven therapies to avoid clinical progression into severe advanced stages where host-immune inflammatory response is the most important component [21].

Several studies demonstrate that cells infected by coronavirus (CoV) produce elevated levels of PICs in order to tackle the invading virus. The overproduced PICs may cause immuno-mediated damage to the lungs and other organs, resulting in severe lung injury and systemic hyperinflammatory syndrome [22]. Once this excessive inflammatory response has been triggered, it may self-perpetuate in some patients despite a decrease in the CoV viral load. So, it may be necessary to add "anti-inflammatory" treatments such as corticosteroids, anti-IL-6 or anti-IL-1 inhibitors, Janus kinase (Jak) inhibitors, polyclonal immunoglobulins, etc. to reduce the secondary deleterious inflammatory response triggered by the virus [6].

In this regard, glucocorticoids appear as a key first-line option, especially given their worldwide availability and cost. However, their use has been controversial in patients with SARS-CoV, MERS-Cov or influenza infections. On the one hand, intravenous steroid use has been associated with delayed elimination of coronaviruses in the blood and lungs of patients with MERS-CoV [23] and SARS-CoV [24], and steroids associated with an increased risk of mortality and adverse events in influenza patients [[25], [26], [27]]. On the other hand, a Cochrane review of glucocorticoids as adjunctive therapy in influenza found evidence of low quality due to confounding by indication [28], and there are some series which suggest improvement of severe COVID-19 lung injury after administration of steroids [8,10].

Furthermore, a small retrospective observational study conducted in China [29] suggests the efficacy of tocilizumab (an IL-6 inhibitor) in the treatment of 21 COVID-19 patients with severe pneumonia and high IL-6. But tocilizumab can cause even deeper immunosuppression than steroids, increasing the risk of sepsis, bacterial pneumonia, gastrointestinal perforation, and hepatotoxicity [20]. Another drawback of tocilizumab is its shortage in some hospitals worldwide and its high cost to national health systems. Interestingly, IL-1 blockade has shown particular promise in cytokine storm syndrome and high-dose regimens have been shown safe even in the context of overt sepsis [30]. Emapalumab (anti-IFNγ) is FDA-approved for HLH and may be effective in COVID-19 inflammatory phase. JAK inhibition appears promising; however, the safety of this medication in severe viral infection remains unknown. Accordingly, some ongoing RCTs are studying glucocorticoids and blockage of IL-1, IL-6, and IFNγ in COVID-19 [6]. However, at the end of April 2020, no trials assessing calcineurin inhibitors, whether tacrolimus or cyclosporine, had been registered either at www.clinicaltrials.gov nor EU Clinical Trials Register, thus prompting us to carry out the present investigation.

Given the scarcity of medical reports supporting the use of immunosuppressive therapy in severe COVID-19, the TACROVID trial was initiated on March 29, 2020. The study is a pragmatical, randomized, open-label, single-center, phase II clinical trial to evaluate the effectiveness and safety of methylprednisolone and tacrolimus in combination regimen plus SoC, versus SoC alone, in COVID-19 with severe lung injury and systemic hyperinflammatory syndrome. We decided to consider methylprednisolone pulses for their rapid onset of action, combined with the ability of tacrolimus to inhibit both the multiple PICs, and the SARS-CoV replication in cell cultures. Moreover, the rationale of our study is aligned with an Ovid MEDLINE review article [13] searching for current evidence for immune-suppressing or stimulating drugs to treat COVID-19, which concludes that low-dose methylprednisolone and tacrolimus may have a beneficial impact in such COVID-19 populations.

Tacrolimus has been administered for decades to prevent allograft rejection in transplanted patients as well as to treat patients with severe autoimmune diseases, and it has a well-known safety profile. In addition, it is a low-cost drug and can be manufactured on a large scale. Thus, if tacrolimus is effective in treating the inflammatory process triggered by COVID-19, a large number of patients could be treated in developed and developing countries. Despite the fact that tacrolimus has been shown to be safe for other diseases, we [researchers] are particularly aware of the possible occurrence of associated AE throughout the present TACROVID trial. In this respect, most patients in the advanced stage of the COVID-19 illness are currently given on immunosuppressive treatment and it is well-known that this facilitates certain opportunistic infections, making it difficult to attribute them to one particular drug. Moreover, the drawback of tacrolimus is that it may interact with some antiviral treatments used in COVID-19 (especially Lopinavir). Finally, tacrolimus is started when patients transition into the most severe clinical stage which, in turn, facilitates the occurrence of AE.

Interestingly, in addition to its immunomodulatory effect, tacrolimus has been also reported to show certain in vitro activity against different human coronaviruses, inhibiting viral replication through immunophilins, although its efficacy and safety have not been assessed in clinical practice. For this reason, an interim analysis will be conducted when half of patients (21 per arm) will be recruited in order to measure the basal and weekly viral load, and the potential AE related to immunosuppression.

Regarding the study design, the present trial was not designed as a double-blind trial. This was considered unrealistic given the emergency situation and the extensive workload that it would involve for the hospital pharmacy service. For the above-mentioned reasons, the TACROVID trial was designed as an open study which allows the use of all drugs that treating physicians prescribe, even without clear evidence to support their use. To minimize the impact of an open study, the primary end-point “time to clinical stability”, is based on objective, quantitative measures for 48 consecutive hours: body temperature, and PaO2/FiO2 and/or SatO2/FiO2, and respiratory rate. Likewise, the statistician performing analysis is blind to the treatment that patient receives (experimental vs control).

Cytokine measurement throughout the trial can reveal new available information on COVID-19 evolution and potential new treatment targets. IFNγ and IL-1β are very relevant cytokine in MAS, but they are not easily assessed in the peripheral blood. CXCL9, a stable chemokine, is a useful surrogate for IFNγ activity in MAS, as are IL-18 and IL-1RA for IL-1β. Thus, in this trial we will not only analyse how the cytokine profile evolves after treatment with tacrolimus, but we will also be able to detect increases in cytokines that can also be treated by other proven specific inhibitors (e.g. IL-18 with Tadekinig alpha, IFNγ with Emapalumab).

In summary, the TACROVID trial assesses the combined use of tacrolimus and methylprednisolone, in addition to the standard of care in patients with severe COVID-19 illness. The aim is to evaluate both the beneficial effect of tacrolimus on controlling viral replication and, in combination with methylprednisolone pulses, modulating the host-immune inflammatory response triggered by the virus. In addition, potential adverse events related to this immunosuppressive therapy are carefully followed-up throughout the investigation. The results of the present trial might encourage further RCTs to assess the efficacy and safety of new antiviral and anti-inflammatory drugs regimens, in sequential combination, at earlier clinical stages of COVID-19.

